#### 1) VOTOR registry data

The VOTOR registry is the largest and most comprehensive orthopaedic trauma outcomes registry worldwide and is compliant with the ACSQHC operating principles for clinical quality registries. For patients hospitalised >24h for their wrist fracture, cases will be identified through VOTOR using the relevant ICD-10-AM diagnosis codes for the admission. Demographic, injury event, injury diagnosis (ICD-10-AM), procedures (ACHI), in-hospital outcomes, limited implant data, X-ray images, text reports from radiology and surgery, and patient-reported outcome measures (PROMs) will be extracted for all eligible patients for this study. The PROMs are collected prospectively via telephone interview at 6-, 12- and 24-months post-injury [34], and include the 12-item World Health Organization Disability Assessment Schedule (WHODAS), 5-level EQ-5D (EQ-5D-5L), numerical rating scale for pain, pain location, return to work and work disability questions. Follow-up rates exceed 80% at each time point. Linkage with the Victorian Registry of Births, Deaths and Marriages (VBDM) is used to identify post-discharge deaths.

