### Aim 2: Prediction modelling

The performance of models including the AI predicted indicators from the deep learning models will be tested against models including standard registry information using the linked VOTOR registry data (data source 4)). The capacity of the AI indicators to predict outcomes of clinical and post-operative complications, and PROMs post-injury. This will enable us to determine which radiological features based on the X-rays and text reports improve prediction over the standard data available in the registry. AI-derived fracture predicted probabilities and classes will be added to the VOTOR registry data and sent to the CVDL for the Linked VOTOR data. This linked dataset will provide a comprehensive longitudinal dataset for the prediction models.

The capacity of the AI derived fracture characteristics to predict outcome compared to the Linked VOTOR registry data alone will be tested using the following outcomes:

Fracture management complications: implant failure; non-union; mal-union of the fracture; infection; neurological injuryReadmission to hospital for fracture managementPresentation to the ED for fracture-related issuesPatient-reported outcomes at 6-, 12-, and 24-months after injury: EQ-5D-5L; 12-item WHODAS; pain scores; return to work and work-related disability.

A systematic approach to variable selection and model predictive performance will be implemented (Fig 1). Models will investigate predictive pathways and risk of outcomes of interest. State of the art longitudinal machine learning (ML) models [44] will be used for both the variable selection and prediction stages. The large number of covariates raise potential multicollinearity issues, and the possibility of unstable estimates. Therefore, where applicable a number of ML penalized regression methods will be implemented to reduce covariate numbers. The analyses will account for correlated and clustered responses to perform the variable reduction and prediction tasks.

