Linear and generalized linear mixed models (LMMLasso/GLMMLasso) [45], longitudinal multi-level factorization machines model (LMLFMM) [46], longitudinal support vector regression (LS-SVM) [47] and mixed effects random forest (MERF) [48] will be used as these machine learning techniques can handle longitudinal data and a large number of potentially correlated features. The inclusion of predictions from Aim 1 will incorporate associated error that potentially compounds further error with their inclusion in the predictive models, so we will use several measures to review model performance. All models will be summarised by the predictive performance measures of accuracy, precision and recall [49] to select the best performing model for each outcome, and quantify the impact of the inclusion of the AI variables over registry data alone.

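### Accuracy, precision and recall are fixed for every Aim 2 model, but they are undefined for EQ-5D-5L, WHODAS and pain scores unless those scores are first put into classes, and the visible text defines none.

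*Protocol article*

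**What the plan says.** Under Aim 2: Prediction modelling, the article announces multiple performance measures because error in the Aim 1 predictions may carry forward: "so we will use several measures to review model performance". It then names them: "All models will be summarised by the predictive performance measures of accuracy, precision and recall". Their purpose is stated in the same sentence: "to select the best performing model for each outcome, and quantify the impact of the inclusion of the AI variables over registry data alone".

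The patient-reported outcomes in the same section are "EQ-5D-5L; 12-item WHODAS; pain scores; return to work and work-related disability", at 6, 12 and 24 months. The VOTOR registry data section describes the instruments as "12-item World Health Organization Disability Assessment Schedule (WHODAS), 5-level EQ-5D (EQ-5D-5L), numerical rating scale for pain".

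The candidate learners include "Linear and generalized linear mixed models (LMMLasso/GLMMLasso") and "longitudinal support vector regression (LS-SVM"). The text does not say which learner goes with which outcome.

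**The concern.** Precision and recall are proportions taken from a table of predicted against observed classes, and accuracy in that company is the proportion classified correctly. A model that predicts a WHODAS score or a pain rating as a number produces no such table. The rule covers all models and each outcome, so it reaches these scores as well as the event outcomes it suits.

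The same measures carry the Aim 2 answer, namely how much the AI-derived characteristics add to registry data. If they are undefined for a score, the analyst must either depart from the stated rule or create categories. In the second case the size of the AI gain depends on a choice that the visible text leaves open, and a small true gain becomes harder to see.

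**Working it through.** **1. The plan's own figure.** The article gives no numerical target for Aim 2 performance, so there is nothing to reproduce on this point. Its one calculated sample size, 517, belongs to Aim 1. It reproduces as 155/0.30 = 516.7, rounded up, from an exact binomial test of 0.7 against 0.8, if one-sided alpha is taken as 0.025. Nothing below depends on it.

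**2. Which outcomes are affected.** Aim 2 lists five complications, readmission, ED presentation and five patient-reported items: 5 + 1 + 1 + 5 = 12. The measures suit the complications, readmission, ED presentation and return to work. The scale of work-related disability is not described. EQ-5D-5L, WHODAS and pain are scores, so 3 of 12 outcomes are affected, each at three time points.

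**3. Is a class defined for them?** The visible text gives no cut-point, responder definition or ordered category for these three, and no error measure for a numeric outcome. Linear mixed models and support vector regression point to numeric responses being foreseen.

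**4. Does the choice of cut matter?** Assumed example: standard normal outcome, registry coefficient 0.5, AI coefficient 0.25, 200,000 simulated patients, and a patient classed as high when the predicted probability exceeds 0.5. On the original scale RMSE falls from √(1 − 0.25) = 0.866 to √(1 − 0.3125) = 0.829, one answer whatever the cut. After a split:

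| Cut (percentile) | Gain in accuracy | Gain in precision | Gain in recall |
|---|---|---|---|
| 50th | +0.023 | +0.024 | +0.022 |
| 70th | +0.014 | +0.022 | +0.069 |
| 80th | +0.007 | +0.021 | +0.065 |
| 90th | +0.001 | −0.001 | +0.032 |

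The same AI contribution looks useful or absent according to the cut and the measure.

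**5. How much information could be lost?** None of these inputs is a plan figure except where noted. Assume a normal outcome with variance 1, registry R² = 0.20, AI gain g, known coefficients, one time point, a median split and a test at z > 1.96. Take n = 4,800, which is 80% of 6,000: the article gives more than 6,000 VOTOR cases and follow-up above 80%.

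*Squared error.* The paired difference has mean g and variance 2g² + 4g(1 − 0.20 − g). For g = 0.02 the variance is 0.0008 + 0.0624 = 0.0632 (SD 0.2514). The expected z is √4,800 × 0.02/0.2514 = 5.51, and the detection probability is Φ(5.51 − 1.96), above 0.99.

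*Accuracy.* At a median split accuracy is 1/2 + arcsin(√R²)/π. This gives 0.6476 at R² = 0.20 and 0.6554 at 0.22, a difference of 0.0078. The two models disagree in a proportion arccos(√(0.20/0.22))/π = 0.0975 of patients. The expected z is √4,800 × 0.0078/√(0.0975 − 0.0078²) = 1.73, and the detection probability is Φ(1.73 − 1.96) = 0.41. Simulation with 1,500 replicates gave 0.42.

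The same formulas with other inputs:

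| n | Gain in R² | Squared error | Accuracy |
|---|---|---|---|
| 4,800 | 0.01 | 0.97 | 0.18 |
| 4,800 | 0.02 | >0.99 | 0.41 |
| 4,800 | 0.03 | >0.99 | 0.65 |
| 4,800 | 0.05 | >0.99 | 0.93 |
| 960 | 0.02 | 0.69 | 0.12 |

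The last row supposes a 20% test set (0.20 × 4,800 = 960). The 20% hold-out under Power calculations concerns the paired image and text data, so applying it to Aim 2 is also an assumption.

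**The case against.** The strongest defence is that the article is condensed. It refers to Fig 1 for its analysis plan and its approach to predictive performance, and that figure is not shown. Score categories or further error measures may stand there or in a fuller plan. This stands as a limit on the claim, since the absence of cut-points can be asserted only of the visible text. It does not remove the mismatch, because the written rule covers all models and any addition would have to be reconciled with it.

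A second defence is that accuracy may be meant loosely, as closeness of prediction. Possibly so, but precision and recall, named beside it, cannot be read that way for a numeric prediction.

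A reader might infer several stronger points that the documents do not support:

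- *That splitting each score in two is the only literal way to comply.* It is not. The three measures also exist for several classes, and EQ-5D-5L levels or pain ratings could be handled as ordered categories. The article never calls these outcomes continuous.
- *That half of Aim 2 is affected.* Three of twelve listed outcomes are affected, though patient-reported outcomes are named in the aim itself.
- *That a real AI gain would usually be missed.* The detection figures rest on an R², a gain, a split and a test that appear nowhere in the article. At a gain of 0.05 and n = 4,800, accuracy detects it with probability 0.93. At n = 960 and a gain of 0.02, squared error itself misses about 30%.

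**Conclusion.** The point holds as a stated rule that does not fit three of the outcomes it covers. For EQ-5D-5L, WHODAS and pain, the comparison of models with and without AI variables is undefined in the visible text unless the scores are categorised, and no categories are given there. This conclusion follows from the definitions and needs no simulation.

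The size of the consequence does rest on assumptions. In the assumed example of step 4, the accuracy gain runs from about 0 to 0.023 depending on the cut. Under the step 5 inputs at n = 4,800 and a gain of 0.02, detection drops from above 0.99 to about 0.4. The loss shrinks as the true gain grows, and repeated measures at three time points are not modelled.

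Severity: SHOULD-FIX. This is a registry prediction study, the event outcomes and return to work are unaffected, and the remedy needs no new data.

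**What to change.** Amend the performance-measure sentence under Aim 2: Prediction modelling so that measures are assigned by outcome type:

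- **Categorical outcomes** (complications, readmission, ED presentation, return to work): keep accuracy, precision and recall. State how work-related disability is scaled and place it accordingly.
- **EQ-5D-5L, 12-item WHODAS and pain:** compare models with and without the AI variables on the original scale, by out-of-sample R² and RMSE or MAE at 6, 12 and 24 months, giving the paired difference with its confidence interval.
- **Any categorised analysis of these scores:** make it secondary, with the categories fixed in advance.

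If Fig 1 or a fuller plan already assigns measures or categories, bring the sentence into line with it. The cost is one sentence and minor programming.

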### Data security and confidentiality

Electronic data including images will be transferred from the participating sites to Monash University through a Secure File Transfer Protocol (SFTP) set up for this project. Once received at Monash, all data will be curated and analysed using the Monash Secure eResearch Platform (SeRP) and the Multimodal Australian ScienceS Imaging and Visualisation Environment (MASSIVE) platform. Monash SeRP is a secure environment for sharing research data for collaboration and analysis, within the control and governance of the data custodian. MASSIVE is a specialised high-performance computing facility for imaging and visualisation which has hardware dedicated to deep learning type applications (a pool of NVIDIA DGX1-V servers). Both SeRP and MASSIVE operate in ISO27001 compliant environments. Risks to patient privacy and confidentiality will be minimised through the use of specific study IDs and collated data will have identifiers removed. Only aggregate data will be presented.

## Discussion

Distal radius (wrist) fractures are the most common fracture presenting for medical care across all age groups. The anatomical pattern of injuries is diverse, there is widespread variation in clinical management, guidelines for management remain inconclusive, and the uptake of findings from clinical trials into routine practice has been limited. Robust predictive modelling which considers the characteristics of the fracture provides the best opportunity to inform care pathways and improve outcomes for patients. However, much of the data about the characteristics of the fracture is in unstructured data sources (x-ray images and text reports) which are not considered easily accessible and has made it difficult and restrictive for researchers to use in predictive modelling. This project will use existing data to assess the role of AI techniques to determine whether information gleaned from images and text reports can improve the prediction of clinical and longer-term patient reported outcomes following wrist fracture. Prediction models based on routinely collected registry data will be compared with models based on registry data and enhanced with additional information about fracture characteristics from the artificial intelligence techniques. The findings of this study have the potential to improve the automated collection of key information about fractures to support clinical decision making, guide personalised fracture care and improve outcomes for patients with wrist fractures by improving predictive models.

## Conclusion

In this study, the role of AI deep learning will be explored to determine whether AI techniques can improve the prediction of clinical and longer-term patient reported outcomes following distal radius fracture. The flexible three-stage multimodal deep learning fracture reasoning system will be used to extract important information from unstructured data sources including X-ray images, surgical and radiology text reports. Using existing data, prediction models with and without the AI enhanced findings from the deep learning system will be compared in order to enhance the capability of clinical registries to generate predictive analytics capable of guiding personalised fracture care.

## List of abbreviations

ACHI: Australian Classification of Health Interventions
ACSQHC: Australian Commission on Safety and Quality in Health Care
AI: Artificial Intelligence
BERT: Bidirectional Encoder Representations from Transformers
CNN: Convolutional Neural Network
DL: Deep Learning
DLFRS: Deep Learning Fracture Reasoning System
ED: Emergency Department
EMR: Electronic Medical Record
EQ-5D-5L: EuroQol- 5 Dimension 5-level
GLMM: Generalized linear mixed model
ICD-10-AM: International Classification of Diseases, 10th Revision, Australian Modification
LMM: Linear mixed models
LS-SVM: Longitudinal support vector regression
MERF: Mixed effects random forest
ML: Machine Learning
MLFMM: Longitudinal multi-level factorization machines model
NLP: Natural Language Processing
PROMs: Patient-reported outcome measures
SAIL: Secure Anonymised Information Linkage
SeRP: Secure eResearch Platform
TAC: Transport Accident Commission
UK: United Kingdom
US: United States
VAED: Victorian Admitted Episodes Dataset
VEMD: Victorian Emergency Minimum Dataset
VBDM: Victorian Registry of Births, Deaths and Marriages
VOTOR: Victorian Orthopaedic Trauma Outcomes Registry
WHODAS: World Health Organization Disability Assessment Schedule
